#### Sample size calculation

*Primary Outcome:* To find a difference in the mean score on the PHQ-9 or GAD-7 of 3-points (from 13 to 10), with a standard deviation of 5-points, power of 90%, an alpha level of 0.05, and 20% loss to follow-up (based off of previous mortality rates in the study ICUs [local data]), 72 dyads per group are required (*N* = 144). *Secondary Outcomes:* To find a difference in the proportion of delirium events reported in the medical chart (most conservative estimate based on secondary outcomes selected) of 20% (from 10 to 30%) at 90% power, an alpha level of 0.05, and 20% loss to follow up, 99 dyads per group are required (*N* = 198). The primary outcome requires a smaller sample size, and thus the most conservative number based on a secondary outcome is employed here.

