**Methods:**

The primary aim of this study is to determine the effect of family-administered delirium prevention, detection, and management in critically ill patients on family member symptoms of depression and anxiety, compared to usual care. One-hundred and ninety-eight patient-family dyads will be recruited from four medical-surgical ICUs in Calgary, Canada. Dyads will be randomized 1:1 to the intervention or control group. The intervention consists of family-partnered delirium prevention, detection, and management, while the control group will receive usual care. Delirium, depression, and anxiety will be measured using validated tools, and participants will be followed for 1- and 3-months post-ICU discharge. All analyses will be intention-to-treat and adjusted for pre-identified covariates. Ethical approval has been granted by the University of Calgary Conjoint Health Research Ethics Board (REB19–1000) and the trial registered. The protocol adheres to the Standard Protocol Items: Recommendations for Interventional Trials (SPIRIT) checklist.

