## Background

Patients admitted to the Intensive Care Unit (ICU) are the sickest in the healthcare system; they have complex medical problems that require urgent treatment with life sustaining technologies [1]. Within this context, one of the largest challenges in the care of critically ill patients is the development of delirium. Delirium (an acute confusional state characterized by fluctuating course, attention deficits, and severe disorganization of behavior [2]) is present in over half of all critically ill patients admitted to ICUs [3–8]. Delirium is associated with negative outcomes in critically ill patients, including longer hospital stays [9], increased risk of long-term cognitive impairment, and death [10–12].

Family members of critically ill patients are also exposed to high levels of stress and are at risk of developing stress-related complications during and after the ICU stay, including sleep disturbances, anxiety, and depression [13]. Witnessing delirium is distressing for families, who watch their loved one's suffering both during and after a hospital stay [14]. Families are essential to the journey of critically ill patients and their participation in care may improve outcomes for both patients and families [15–18]. For example, there was a decrease in symptoms of both anxiety and depression in families who witnessed cardiopulmonary resuscitation [16] and those who received information on what to expect at the end of life [17]. Family involvement in preventing, detecting, and managing delirium has the potential to produce similar positive effects. The *Facilitated Sensemaking* framework [19–21] provides a theoretical basis for patient- and family-oriented studies in the ICU; engaging families in decision making and care provision may enhance their ability to cope with a new and challenging situation. Patients may also benefit from greater inclusion of family members in the ICU. Increased family presence does not increase infection rates [22, 23] or adverse events [23] and may decrease cardiocirculatory complications [24] and reduce patient falls [25]. Delirium is a common and serious complication of critical illness that affects both patients and their family members. ICU patients, family members, providers and decision-makers (ICU stakeholders) recognize the enormity of this issue and stakeholder groups have identified delirium detection and management as a top quality improvement opportunity [26–30].

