#### Secondary aims

To determine the effect of family-administered delirium prevention, detection, and management in critically ill patients on family member symptoms of psychological distress, compared to usual care.To determine the effect of family-administered delirium prevention, detection, and management on the prevalence (ever/never delirium as indicated by an Intensive Care Unit Delirium Screening Checklist [ICDSC] score ≥ 4), duration (total days of an ICDSC score ≥ 4), and severity of delirium (as indicated by the ICDSC score, which ranges from 0 to 8) in critically ill patients, compared to usual care.To determine the effect of family-administered delirium prevention, detection, and management on the diagnosis of the patient with delirium (ICDSC score ≥ 4), compared to usual care.To determine the effect of family-administered delirium prevention, detection, and management on family member knowledge of delirium in critically ill patients, compared to usual care.To determine the effect of family-administered delirium prevention, detection, and management on the burden of delirium (e.g., feelings of helplessness) experienced by family members of critically ill patients, compared to usual care.

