### Statistical analysis plan

All data will be analyzed as intention to treat. Descriptive statistics will be used to summarize the patient and family characteristics. For all analyses, we will consider a two-tailed *p*-value < 0.05 to be statistically significant, and will adjust for multiple comparisons (Bonferroni correction) in the primary analysis where appropriate. For the secondary aims, we will not correct for multiple comparisons with statistical procedures, but rather consider them in our interpretation. Subgroup analyses and a priori *covariates* to be considered are: presence of mechanical ventilation, RASS score, delirium subtype, patient frailty status (based on Clinical Frailty Scale scores), patient age, patient sex, caregiver age, caregiver sex, and baseline levels of symptoms of depression, anxiety, and psychological distress. Linear regression models will be used to assess for effect modification and confounding. Missing data will be tabulated for all outcomes. If more than 5% of outcome data is missing, multiple imputation will be employed; for the primary aim, we will also conduct a sensitivity analysis assuming the data is missing not at random.

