For the primary aim, we will report a difference in proportion of the clinically significant symptoms of depression [PHQ-9] and anxiety [GAD-7], mean PHQ-9 and GAD-7 scores, and frequency of categories of depression and anxiety (i.e., minimal, mild, moderate and severe) (at discharge from ICU, 1-, and 3- month follow-up) between control and intervention groups. For secondary aims we will report: 1) A difference in proportion of the most severe family members symptoms of psychological distress [K-10] (at discharge from ICU, 1-, and 3- month follow-up) between control and intervention groups. 2) Prevalence of delirium: Difference in proportion of patients with clinical delirium (ICDSC score ≥ 4) pre-post intervention (in-ICU) between control and intervention groups. Duration of delirium: Difference in mean days with clinical delirium (ICDSC score ≥ 4) pre-post intervention between control and intervention groups (in-ICU). Duration of delirium-free days: Difference in mean days without delirium on the ICDSC pre-post intervention between control and intervention groups (in-ICU). Severity of delirium: Difference in most severe ICDSC scores pre-post intervention between control and intervention groups (in-ICU). 3) Difference in the diagnosis of delirium in the medical chart, compared to usual care (when appropriate, i.e., when delirium is present) pre-post intervention between control and intervention groups (in-ICU). 4) Difference in mean CIDKQ scores pre-post intervention between control and intervention groups (in-ICU). 5) Difference in mean DEL-B scores pre-post intervention between control and intervention groups (in-hospital). The statistical significance of the differences between proportions or means (between the intervention and control groups) will be calculated using the.

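### N = 198 is sized on charted delirium counted over all dyads but analysed only among patients with delirium, and the stated 90% power is not secure on either count

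*Protocol article*

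**What the plan says.** In the Protocol article, the section Sample size calculation gives two results. The primary outcome needs 72 dyads per group (N = 144). The larger number, which the trial adopts, comes from a secondary outcome: "a difference in the proportion of delirium events reported in the medical chart" "of 20% (from 10 to 30%) at 90% power", at alpha 0.05, "and 20% loss to follow up, 99 dyads per group are required" (N = 198).

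The Statistical analysis plan describes that outcome under secondary aim 3 as "Difference in the diagnosis of delirium in the medical chart, compared to usual care". It then adds in brackets that this applies where delirium is present. The calculation has no matching restriction or allowance.

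Under Secondary aims, aim 2 begins "To determine the effect of family-administered delirium prevention, detection, and management on the prevalence", defined as ever or never reaching an ICDSC score of 4 or more; duration and severity follow. The Background says that delirium "is present in over half of all critically ill patients admitted to ICUs".

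**The concern.** One intervention is meant both to prevent delirium and to get it recognised. If charted delirium is counted over all patients, these two effects pull in opposite directions: better recognition raises the proportion and fewer cases lower it. The sample size assumes a rise of 20 points and does not say whether that is before or after any prevention effect.

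If the outcome is instead counted only among patients with delirium, the proportion need not fall, but two other problems appear. The number of analysable patients is well below the number used in the calculation. The comparison is also restricted by a state that arises after randomisation and that the intervention may change, so the groups compared are no longer the randomised groups.

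At stake is the power claim for the one outcome that justifies the step from 144 to 198 dyads. So is the reading of a weak aim 3 result, which could reflect unchanged recognition or less delirium to recognise.

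**Working it through.** **Inputs from the Protocol article.** Rates 10% and 30%, power 90%, 20% loss, 99 per group (Sample size calculation); two-sided 5% level, "we will consider a two-tailed *p*-value < 0.05 to be statistically significant" (Statistical analysis plan); equal allocation, "Dyads will be randomized 1:1 to the intervention or control group" (Abstract, Methods).

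**Assumptions, not in the document.** Control prevalence of 50%, or 70% as a second case, as illustrations around the Background's statement; only true cases are charted; prevalence reductions of 0 to 20 points. Evaluable patients per arm run from 79 (99 × 0.8) to 99 (no loss, since the outcome is collected in the ICU).

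**1. Reproduce the plan's figure.** n = (1.960 + 1.282)² × (0.10 × 0.90 + 0.30 × 0.70) / 0.20² = 10.507 × 0.30 / 0.04 = 78.8 per arm. 78.8 / 0.8 = 98.5, rounded up to 99. The pooled-variance formula gives 82 per arm, and 82 × 1.2 = 98.4 also rounds up to 99. Both routes count every dyad. Neither has a factor for the share of patients with delirium.

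**2. All dyads in the denominator.** Charted proportion = prevalence × share of cases charted. With 50% prevalence in both arms, 10% v 30% corresponds to charting of 0.10/0.50 = 20% v 0.30/0.50 = 60% of cases. Hold 60% fixed and lower the prevalence in the intervention arm. Power is exact for the two-sided uncorrected chi-square test at 0.05:

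| Reduction in prevalence | Charted, intervention | Power, 79 per arm | Power, 99 per arm |
|---|---|---|---|
| 0 points | 50% × 60% = 30% | 90% | 95% |
| 5 points | 45% × 60% = 27% | 81% | 89% |
| 10 points | 40% × 60% = 24% | 67% | 76% |
| 20 points | 30% × 60% = 18% | 31% | 37% |

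The normal approximation at 79 per arm gives 89%, 79%, 65% and 30%, so the pattern does not depend on the method.

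**3. Only patients with delirium in the denominator.** Take 10% v 30% as charting rates among cases, with no prevention effect.

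- Prevalence 50%: 79 × 0.5 = 39.5 and 99 × 0.5 = 49.5 per arm. Exact power is 62% with 39 and 73% with 50.
- Prevalence 70%: 79 × 0.7 = 55.3 and 99 × 0.7 = 69.3 per arm. Exact power is 77% with 55 and 86% with 69.

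Keeping 79 evaluable cases per arm would take 79 / 0.8 / 0.5 = 198 dyads per group at 50% prevalence, or 79 / 0.8 / 0.7 = 142 at 70%. A prevention effect lowers power a little further by shrinking the intervention group. With 40 v 32 cases (a fall from 50% to 40% prevalence, 79 evaluable) it is 59%.

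**4. Primary comparison at N = 198.** Difference 3, SD 5, 79 per arm: (3/5) × √(79/2) = 3.77. Power ≈ Φ(3.77 − 1.96) = 96% at 0.05, and Φ(3.77 − 2.24) = 94% at a Bonferroni level of 0.025.

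**The case against.** The strongest case on the other side has four parts.

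- **The analysis section conditions on delirium.** The sample-size wording, a proportion of delirium events, can be read the same way. A reader might infer that charted delirium must fall whenever prevention works. The document does not support that: among patients with delirium, prevention does not mechanically lower the proportion. This stands, but it does not rescue the 90%, because on that count power is short before any prevention effect (step 3).
- **The 30% may already be net.** Over all dyads, 10% v 30% fits other combinations, such as 50% × 20% v 40% × 75%. A reader might infer that the 90% holds only if the intervention leaves prevalence unchanged. That is also too strong. The document does not say whether 30% is gross or net, and this silence is part of the point.
- **No reduction in prevalence is assumed anywhere.** The hypothesis at the end of the Background names shorter and milder delirium, and neither need change whether a patient is ever charted. This stands as a limit on the size of the problem. Aim 2 nevertheless tests prevalence, and the intervention is described as preventive.
- **Aim 2 is reported alongside aim 3**, so a weak aim 3 result can be read against prevalence. This is true in part. Two separate margins do not show which delirium cases went uncharted, and the plan gives no joint table.

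**Conclusion.** The point holds in a limited form. The sizing counts all dyads, the analysis counts only patients with delirium, and the 90% is not secure under either. Over all dyads it applies to a net 10% v 30%. If the 30% is gross, power is 81–89% with a 5-point reduction in prevalence and 67–76% with a 10-point reduction. Among patients with delirium, it is about 62–73% at 50% prevalence and 77–86% at 70% without any reduction. The prevalences, the 20% v 60% charting rates and the reductions are assumptions, so these are illustrative ranges and not estimates.

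It would go too far to say that the plan's assumptions for aims 2 and 3 contradict each other, because the document states no prevalence assumption for aim 2. The consequence is confined to a secondary outcome. The primary comparison keeps about 94–96% power with 79 evaluable per arm.

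**What to change.** 1. **One denominator.** In both the Statistical analysis plan and the Sample size calculation, define aim 3 over all randomised patients. This keeps the randomised comparison and matches the existing arithmetic. The sponsor should first confirm that 10% and 30% are rates on that denominator. If they were meant as rates among cases, they must be converted: at 50% prevalence they become 5% v 15%, and the sample size has to be recalculated.
2. **A joint table.** Report delirium yes/no (ICDSC 4 or more) by charted yes/no in each arm, over all randomised patients, so that prevention and detection can be told apart.
3. **A supportive outcome.** Add missed delirium (ICDSC 4 or more and not charted) over all randomised patients. Prevention and better charting both lower it. It should not replace aim 3: it changes the question, still mixes the two effects, and has 80–88% power for 40% v 20% (the step 2 assumptions, no prevention effect).
4. **Qualified power.** State that 90% applies to a net 10% v 30% over all dyads, and show the lower figures as a range with their assumptions.

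The cost is wording in the protocol and the analysis plan. The ICDSC and the chart are already data sources, and no added recruitment follows if 10% v 30% is confirmed as the net all-patient contrast. The drawbacks are a less favourable stated power and continued reliance on the nurse-scored ICDSC.

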### Dissemination

Given the study carries minimal risk, a data safety and monitoring board has not been established. Team members (including patient advisors and trainees) will present the results of this work to a variety of knowledge users, including researchers and clinicians at research rounds and the public at open engagement sessions (e.g., Café Scientifique [37]) and patient-identified forums of interest. Traditional dissemination strategies will include the publication of results in a peer-reviewed journal and educational sessions, while we will employ non-traditional dissemination strategies including blog and social media posts targeted at a public audience. The study design adhered to the Standard Protocol Items: Recommendations for Interventional Trials (SPIRIT) checklist [57]. Any modifications to the protocol will be agreed upon by all protocol authors and approved by the ethics board prior to implementation.

### Registration

This study is registered on clinicaltrials.gov (NCT04099472).

### Study and data management

The coordinating centre for the study is the FMC in Calgary, Canada. Local investigators at each site will be responsible, along with a study coordinator, for day-to-day operations. Data will be managed in a REDCAP database created for this project and stored on a secure institutional network drive. Hard copy materials will be stored in a secure locked office in a locked cabinet. All data will only be accessible by study personnel.

## Discussion

Previous research demonstrates that family members of critically ill patients want to assist with nonpharmacological delirium prevention activities, but most family members do not possess enough delirium knowledge to be effective partners [58, 59]. A study by Black et al. reported family participation in psychological care does not improve the incidence of delirium [60]. These data will help us understand the effect that a family member’s participation in delirium prevention, detection and management will have on family-centered psychological outcomes.

The primary limitation for the ACTIVATE study is loss to follow-up after ICU discharge, which would threaten the internal validity of our findings through selection bias, should those who remain differ from those who are lost. Our experience recruiting in this population will help mitigate this issue; specifically the inclusion of patient advisors as recruiters, which we have found increases response rates dramatically (from 23% [39] to 75% [42]). Questionnaire completion will depend on the timing and availability of family members, thus missing data may also present a threat to our study through selection bias. We will ensure flexible opportunities for questionnaire completion to facilitate data capture and employ methods to impute missing data where appropriate. The burden of completing the questionnaires presents an additional limitation to the study; we have piloted the questionnaires with patient researchers on our team to ensure the length is manageable (average time less than 20 min).

## Data Availability

The study protocol is registered on clinicaltrials.gov (NCT04099472) and data and statistical code will be shared given reasonable requests to the corresponding author.

## Abbreviations

APACHE: Acute Physiology and Chronic Health Evaluation
BCQ: Barriers to Care Questionnaire
CCFNI: Critical Care Family Needs Inventory
CIDKQ: Caregiver ICU Delirium Knowledge Questionnaire
CONSORT: Consolidated Standards of Reporting Trials
CSS: Coping Strategies Scale
DEL-B: Delirium Burden Scale
DSM: Diagnostic and Statistical Manual of Mental Disorders
FAM-CAM: Family Confusion Assessment Method
FMC: Foothills Medical Centre
GAD: Generalized Anxiety Disorder
GAD-7: Generalized Anxiety Disorder-7 Item
ICDSC: Intensive Care Delirium Screening Checklist
ICU: Intensive Care Unit
K-10: Kessler-10
NCT: National Clinical Trial
PHQ-9: Patient Health Questionnaire-9 Item
PLC: Peter Lougheed Centre
RASS: Richmond Agitation and Sedation Scale
REB: Research Ethics Board
RGH: Rockyview General Hospital
SHC: South Health Campus
SOFA: Sequential Organ Failure Assessment
SPIRIT: Standard Protocol Items: Recommendations for Interventional Trials
